## Abstract

Supplemental Digital Content is available in the text

## Introduction

1

Breast cancer is the most common female cancer worldwide. In 2018, the Global Cancer Observatory estimated that slightly >2 million new cases of breast cancer were diagnosed in women worldwide and approximately 600,000 patients died from the disease.^[1]^ In Hong Kong, the incidence of breast cancer increased from 1152 in 1993 to 4108 in 2016. On average, about 9 women are diagnosed with breast cancer every day in Hong Kong. These women's median age is 56 years compared to 61 years in the United States and 62 years in Australia. The rising incidence of breast cancer in Hong Kong, particularly in younger women, is attributed to the increased Westernization of Chinese women, particularly in terms of adverse dietary and other lifestyle practices.^[2]^

In estrogen receptor positive (ER+) early-stage breast cancer, 5 years of adjuvant endocrine therapy substantially reduce the risks of locoregional and distant recurrence, contralateral breast cancer, and death.^[3–5]^ Tamoxifen, a selective estrogen receptor (ER) modulator (SERM), is the most frequently used antiestrogen adjuvant treatment for ER+ pre-menopausal women. In trials that compared 5 years of tamoxifen therapy to no endocrine therapy in patients with ER+ breast cancer, the recurrence rate in the tamoxifen group was approximately 50% lower during the first 5 years and approximately 30% lower during the subsequent 5 years. In addition, the mortality rate was approximately 30% lower in the tamoxifen group during the first 15 years.^[4]^ However, tamoxifen had little or no effect on breast cancer recurrence or mortality in ER-negative disease.

To maximize its effectiveness, tamoxifen should be taken at the recommended dose for 5 years. However, effectiveness is predicated on 2 inter-related factors. The first is individual drug metabolism, which affects the response of the cancer to treatment.^[6]^ The second is drug adherence, which is markedly influenced by the type and severity of tamoxifen-related symptoms.^[7]^ Previous studies mainly focused on the impact of genotypes on tamoxifen metabolism and efficacy.^[8,9]^ In view of the importance of drug adherence, a need exists to identify biomarkers that are associated with tamoxifen-related symptoms which affect patients’ level of adherence.

Tamoxifen's endocrine symptom profile can influence patients’ perceptions of the drug's benefits or harms. If symptoms are severe, patients may not adhere to tamoxifen. Common endocrine symptoms associated with tamoxifen include vasomotor symptoms (eg, hot flashes, cold sweats, night sweats), neuropsychiatric symptoms (eg, dizziness, headaches, mood swings, anxiety, depression, insomnia), musculoskeletal symptoms (eg, muscle and joint pain), and sexual dysfunction. These symptoms can be disabling. In 1 study, the most common symptom was hot flashes (64%), with 20% of women reporting severe hot flashes.^[10]^ However, because the type and severity of symptoms are highly variable among patients, clinicians are not able to predict which patients will experience a higher symptom burden.

Adherence rates are usually reported as the percentage of the prescribed dose of the medication actually taken by the patient over a specified period of time.^[11]^ Given the large amount of interindividual variability in tamoxifen-related endocrine symptoms and the need to take the drug daily for 5 years, different adherence rates were reported for different age groups and treatment durations. In 1 study of 5707 patients who took tamoxifen for 5 years, the incidence of nonadherence with tamoxifen in women <35 years of age at 1 year was 11%, increasing to approximately 17%, 23%, and 25% at 2, 3, and 4 years after random assignment. For those ≥35 years of age, nonadherence rates were 9%, 14%, 18%, and 21%, respectively.^[12]^

This evaluation of adherence is important because nonadherence results in higher mortality. For example, estimated survival at 10 years was 80.7% for women who continued hormonal therapy versus 73.6% for those who discontinued it (*P* < .001). Of those who continued, survival at 10 years was 81.7% and 77.8% in women who adhered and nonadhered, respectively (*P* < .001). Adjusting for demographic and clinical characteristics, both early discontinuation (hazard ratio [HR] 1.26, 95% confidence interval [CI] 1.09–1.46) and nonadherence (HR 1.49, 95% CI 1.23–1.81), among those who continued, were independent predictors of mortality.^[13,14]^ In addition, poor drug adherence may lead to disease progression, complications, and additional medical costs.^[15]^ Given the significant survival benefits associated with tamoxifen, understanding the extent of adherence to endocrine therapies and identifying genetic and modifiable factors (eg, forgetting to take medication while travelling) that influence adherence warrant investigation.

Patients with very similar clinical characteristics and prognostic factors at diagnosis, who receive the same tamoxifen regimen, vary substantially in their treatment responses and in the clinical course of their disease.^[16]^ These responses can be partially explained by polymorphisms in three tamoxifen metabolism-related genes: cytochrome P450 enzymes, UDP-glucuronosyltransferase and sulfotransferase, and ATP-binding cassette transporters.

Tamoxifen is metabolized into its more active forms by various cytochrome P450 enzymes (eg, CYP2D6, CYP3A4, CYP3A5, CYP2C9, and CYP2C19).^[17,18]^ The effects of CYP polymorphisms on tamoxifen pharmacokinetics were well studied in Asian countries.^[19,20]^ In addition, the UDP-glucuronosyltransferase (primarily UGT1A8, UGT1A10, UGT2B7 and UGT2B15) and sulfotransferase (primarily SULT1A1) catalyze the conversion of tamoxifen metabolites into excretable forms. Sulfotransferase enzymes catalyze the transfer of a sulfonyl group to nucleophilic groups increasing their solubility and facilitating their excretion.^[21,22]^ Finally, 3 members of the ATP-binding cassette (ABC) transporters, namely, ABCB1 (P-gp/MDR1), ABCC1 (BRCP), and ABCC2 (MRP2), are key players in the drug resistance phenotype. ABCB1 is expressed in 28% to 63% of breast cancers, depending on the methodology applied. Polymorphisms in the genes that encode for these transporter proteins can increase their expression and reduced the effectiveness of tamoxifen.

All of the enzymes and transporters in tamoxifen's metabolic pathway are polymorphic. Thus, inter-individual differences in tamoxifen metabolism contribute to variations in the concentration of metabolites in the serum and the drug's effectiveness.

As part of the proposed study, we hypothesize that the drug's metabolic rate may influence the occurrence and severity of tamoxifen-induced endocrine symptom. Only two studies were identified that support this hypothesis. In the first study of 297 patients with breast cancer who were genotyped for polymorphisms in CYP2D6,^[23]^ compared to poor metabolizers (*P* = .038) and extensive metabolizers (*P* = .011), intermediate metabolizers had significantly higher hot flash severity score after 4 months of tamoxifen treatment. In the second study of 258 patients with breast cancer who were genotyped for polymorphism in CYP2D6 and ABCB1,^[24]^ no association were found between any of the polymorphisms and associated symptoms. A major limitation of this second study is that a valid and reliable assessment tool was not used to collect data on tamoxifen-induced endocrine symptoms. Given the positive results from the first study,^[23]^ additional research is warranted to confirm or refute our hypothesis.

Based on the results of previous studies,^[17,18,23–25]^ potential alleles will be selected to test their relationship with symptoms in breast cancer patients. In this study, we aim to characterize polymorphisms in tamoxifen metabolism associated genes and to evaluate for associations among genetic polymorphisms, endocrine symptoms, and adherence to tamoxifen in Chinese patients with breast cancer.

## Methods

2

### Study design

2.1

This prospective cohort study will recruit patients from the Department of Clinical Oncology in Prince of Wales Hospital in Hong Kong. Patients will be enrolled within 30 days of starting tamoxifen. Patients will complete self-report questionnaires on endocrine symptoms and a saliva sample will be collected at enrolment. At 3, 6, 9, 12, 15, and 18 months after enrolment, data on symptoms and drug adherence will be collected through phone interviews using the same measures. Data collection will end at 18 months because symptoms of tamoxifen therapy appear early and are worst during the first 12 months after the initiation of treatment.^[26]^ Patients’ saliva will be collected during enrolment for evaluation of single-nucleotide polymorphism (SNPs) in genes associated with drug metabolism enzymes and transporters.

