### Patient recruitment

2.2

A total of 200 Chinese women who received primary therapy for breast cancer and commence tamoxifen within the past month will be recruited for this study. The inclusion criteria for the patients are: Chinese women with histologically confirmed estrogen receptor-positive, stage I–III, primary invasive breast cancer treated with definitive surgery and/or chemotherapy and started on tamoxifen (20 mg daily) within the past month. We will exclude patients with other cancers within the last 5 years. In addition, patients who are pregnant or are planning to become pregnant, lactating, treated with investigational drugs within the 4 weeks before enrolment, as well as those who are not able to provide written informed consent will be excluded. The participating hospitals have 600 new cases of breast cancer per year and half of these patients will be prescribed tamoxifen. It is anticipated that 100 to 150 patients will be recruited per year based on our experience with the pilot study.

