### Data analysis

2.7

Data will be summarized using appropriate descriptive statistics. Continuous data will be assessed for skewness and kurtosis and normal probability. Appropriate transformations will be made for skewed variables before entering them into the statistical analysis.

Since an episode of drug adherence might not reflect an overall adherence rate of a medication for an extended duration, a summary measure based on the area under the curve (AUC) of repeated measures of tamoxifen treatment adherence assessed using MMARS over 18 months (ie, specifically at months 3, 6, 9, 12, 15, 18) will be used to quantify overall adherence with tamoxifen treatment. Likewise, the AUC for each of the items on the GCS and the FACT-ES that are measured at enrolment, 3, 6, 9, 12, 15, 18 months will be computed first to obtain an overall measure of the severity of each symptom.

Since some highly correlated items may exist in the GCS and FACT-ES, a principal component factor analysis will be conducted on the AUCs of the GCS and FACT-ES items to identify uncorrelated principal components. These principal components can be regarded as the latent factors that give rise to the reported symptoms. Since no previous evidence exists regarding which symptom has a larger effect on adherence with tamoxifen, equal weighting will be given to each principal component. Then, the standardized factor scores computed using the Anderson-Rubin method of the principal components identified will be summed to quantify the overall severity of the symptoms associated with tamoxifen treatment.

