The genetic factors will be examined as individual SNPs and haplotypes of SNPs from different candidate loci, as appropriate. The distribution of genotypes in candidate SNPs will be tested for Hardy–Weinberg equilibrium (HWE) using Fisher exact test. SNPs in conformation with HWE will be used in regressions analyses to determine their relative contribution to the overall severity of the symptoms associated with tamoxifen treatment with adjustment for potential confounders, including age, menopausal status, stage of cancer at diagnosis, and treatment received. The linkage disequilibrium between SNPs in candidate loci will be analyzed using Haploview (Daly Lab, Cambridge, MA) and haplotypes will be created. The relationships between these haplotypes and overall severity of the symptoms of tamoxifen will be analyzed by the regression-based approach of Zaykin et al^[36]^ after adjusting for potential confounders with the use of a permutation test. Statistical significance will be evaluated using permutations with 10,000 replications. Inflated overall type I error rate will be controlled using the approach of Benjamini and Hochberg.^[37]^ Furthermore, multivariable regression analysis will examine the associations between overall adherence with tamoxifen treatment and overall severity of the symptoms of tamoxifen treatment with adjustment for the above potential confounders. All statistical analyses unless otherwise specified will be performed using SAS release 9.4 (SAS Institute, Cary, NC). All statistical tests will be 2-sided and a *P* value <.05 will be considered statistically significant.

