The optimal management strategy for tamoxifen is one that considers the balance between the drug's potential benefits and adverse effects. The way that tamoxifen is metabolized and its potential toxicities are partially influenced by each patient's genetic makeup.^[43]^ The aim of this study is to determine whether, and how, symptoms of tamoxifen correlate with drug adherence and with polymorphisms in genes that regulate the metabolism of tamoxifen in Chinese breast cancer patients. We hypothesize that patients with more severe endocrine symptoms (ie, psychological, somatic, vasomotor, sexual) are less likely to adhere to tamoxifen treatment. In addition, we hypothesize that a relationship exists between the severity of tamoxifen-induced symptoms and allelic variations in tamoxifen metabolism-related genes. To date, studies have focused primarily on the associations between genetic polymorphisms and tamoxifen efficacy^[44,45]^ and not on the association between these factors and tamoxifen-induced symptoms and subsequent adherence. Adherence could be improved by understanding the factors that are associated with patients who are less likely to adhere and any modifiable factors (eg, barriers and facilitators) to their adherence.^[46]^ This increased understanding could contribute to the development of individualized symptom management interventions for patients who are prescribed tamoxifen, ultimately leading to greater adherence and reduced risks of breast cancer recurrence and death.

This study is significant in that it will provide preliminary evidence on the factors associated with tamoxifen adherence in Chinese breast cancer patients. The results of this study may lead to larger descriptive and interventional studies that will evaluate different approaches to increase tamoxifen adherence rates and its clinical efficacy.

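### The first symptom score is taken up to 30 days into tamoxifen with no pre-drug score or comparator, so the design cannot support attributing symptoms to the drug, and prior symptoms dilute the genotype association

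*Protocol article*

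**What the plan says.** Section 2.1 sets the enrolment window: "Patients will be enrolled within 30 days of starting tamoxifen". Section 2.2 fixes the order of events, since an eligible woman is one "started on tamoxifen (20 mg daily) within the past month". The first symptom assessment is at entry: "Patients will complete self-report questionnaires on endocrine symptoms and a saliva sample will be collected at enrolment". The six follow-up interviews are then counted from enrolment. In justifying the 18-month horizon, 2.1 also says that "symptoms of tamoxifen therapy appear early and are worst during the first 12 months after the initiation of treatment".

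Data analysis (2.7) takes "the AUC for each of the items on the GCS and the FACT-ES that are measured at enrolment, 3, 6, 9, 12, 15, 18 months", extracts principal components from these item AUCs, and has the component scores "summed to quantify the overall severity of the symptoms associated with tamoxifen treatment". The regressions on this score are run with "adjustment for potential confounders, including age, menopausal status, stage of cancer at diagnosis, and treatment received". No prior symptom level is listed.

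The Discussion states the hypothesis that "a relationship exists between the severity of tamoxifen-induced symptoms and allelic variations in tamoxifen metabolism-related genes". The article describes no pre-tamoxifen questionnaire, no recall of earlier symptoms and no untreated comparison group.

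**The concern.** The hypothesis is about symptoms that the drug causes, but no measurement is planned before the drug. Women enter after surgery, chemotherapy or both, and the GCS is a climacteric scale, so many may already have the symptoms it counts. One woman may be assessed on her first day of tamoxifen and another on day 30, although the protocol itself says symptoms appear early. The visit labelled month 3 can fall anywhere from 3 to 4 months after the first dose.

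Two things are at stake. First, a high score cannot be attributed to tamoxifen rather than to what the woman brought with her. No later analysis plan can recover a measurement that was never taken. Second, prior symptoms unrelated to metabolism genes add variance to the outcome and shrink the share that a genotype can explain, and that share is what the sample size is built on. In addition, a woman who starts, develops severe symptoms and stops before she is approached may never enter, and she bears on the adherence hypothesis.

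**Working it through.** **1. The plan's own figure.** Inputs from Sample size estimation (2.4): R² = 0.05, 80% power, 5% level (two-sided per 2.7), 24% attrition. For one predictor, use the F test on 1 and n − 2 degrees of freedom with noncentrality λ = n·R²/(1 − R²). At n = 152, λ = 152 × 0.05/0.95 = 8.0 and power is 0.802. Recruitment is 152/0.76 = 200. Both figures reproduce, so there is no arithmetic error here.

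**2. Dilution of the genotype association.** The documents do not say how much of the score is prior symptoms. Assume that a share s of its variance is prior symptoms unrelated to genotype and left over after the planned covariates. Assume also that the allele explains 5% of the rest. Then R² in the planned score is 0.05(1 − s).

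| s | R² | Power at 152 | n for 80% | Recruited (n/0.76) |
|---|---|---|---|---|
| 0 | 0.050 | 0.80 | 152 | 200 |
| 0.1 | 0.045 | 0.76 | 169 | 223 |
| 0.2 | 0.040 | 0.71 | 191 | 252 |
| 0.3 | 0.035 | 0.65 | 219 | 289 |
| 0.5 | 0.025 | 0.50 | 309 | 407 |

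If the 5% in 2.4 is instead meant as a share of the whole observed score, dilution is already inside it and power stays at 0.80. The corresponding effect on drug-related symptoms must then be larger.

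**3. Weight of the enrolment value.** With seven visits three months apart, trapezoidal weights are 1.5, 3, 3, 3, 3, 3 and 1.5 out of 18. Enrolment carries 1.5/18 = 1/12 (8.3%) of each item AUC. It enters as symptom burden, not as a reference level.

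**4. How far the drug effect may have developed at enrolment.** The documents give no onset curve. Assume an exponential approach to a plateau with time constant τ, and enrolment spread evenly over days 0 to 30. The mean share of the plateau present is 1 − (τ/30)(1 − exp(−30/τ)): 37%, 21% and 15% for τ = 30, 60 and 90 days. On day 30 alone, 1 − exp(−30/τ) gives 63%, 39% and 28%. These describe the enrolment score only. Even with the fastest onset shown, the day-0 to day-30 difference in that one value moves a time-averaged AUC by 0.63 × 1/12 = 5.3% of the plateau effect.

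**5. Early stoppers.** The Introduction cites one-year nonadherence of 9% (35 years and over) and 11% (under 35). Read as a constant hazard (an assumption), the 30-day probability is 1 − (1 − p)^(30/365.25), which is 0.8% and 1.0%. That is 1.5 to 1.9 women per 200. At 20% in the first year, near the one in five quoted in the Discussion for suboptimal adherence, it is 1.8%, or 3.6 per 200. The number is larger if stopping clusters early.

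**The case against.** The best case for the plan has four parts.

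- **No change from baseline is planned.** The outcome is severity on treatment, and for that an on-drug first value is part of the outcome. This stands. A reader might infer from the onset percentages that up to 63% of the effect is lost or that the endpoint is biased by that much. The documents do not support this, because enrolment is 1/12 of each item AUC and 2.7 neither subtracts it nor adjusts for it. For the same reason, the worry that baseline adjustment would remove signal applies only to an analysis the plan does not contain.
- **Genotype is germline.** Prior symptoms bias a genotype association only if the genes are related to symptoms without tamoxifen; otherwise they add noise. This also stands, and a reader who infers a biased association goes beyond the text. For symptoms against adherence, total burden may itself be relevant.
- **Menopausal status and treatment received are covariates.** This helps in part. They are group-level proxies and do not replace a woman's own prior score.
- **The timing offset is small.** Thirty days is about 5% of 18 months (30/548), and no resulting bias has been shown. This stands.

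It would also be too strong to say that no score can be free of the drug. Enrolment on or near day 0 is allowed, and a woman who stops during follow-up may be assessed off treatment. But the plan neither requires nor separates the former, and the latter is not a pre-treatment reference. Nor does 2.2 require current use, so a woman who has started and stopped is not formally excluded.

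**Conclusion.** The gap is real and lies in the design. The hypothesis is about tamoxifen-induced symptoms, but with no pre-drug score and no comparator the data can show only how genotype relates to symptoms present during tamoxifen. The attribution is unsupported whatever the analysis.

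The statistical cost is mainly dilution: power of roughly 0.65 to 0.76 instead of 0.80 if 10% to 30% of the score variance is unexplained prior symptoms. That range rests on an assumed share and on reading the 5% effect as applying to the drug-related part. Missed early stoppers are probably a few women, though plausibly those with the worst early symptoms. The onset percentages are assumption-based and do not measure bias in the planned AUC. The point does not invalidate the study, which the Discussion presents as preliminary evidence. A change is worth making because it is cheap and improves the study's ability to answer its own question.

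**What to change.** **Any remaining recruits.** Amend 2.1 and 2.2 so that women are approached when tamoxifen is prescribed and complete GCS and FACT-ES before the first dose. Adjust the symptom analysis for that pre-dose score and keep it out of the on-treatment AUC. Build the AUC over the same on-treatment period for all women, so that pre-drug and on-drug first points are not mixed.

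**Women already enrolled.** Take the first-dose date from the eligibility check, which needs it, or from the prescription record. Drug adherence (2.5.2) does not say that the diary or refill form captures a dose taken before enrolment. Time visits from that date and include days on tamoxifen at enrolment as a covariate. Run a sensitivity analysis in women enrolled within the first few days of treatment. If enrolment were spread evenly, the first three days would hold about 3/30 × 200 = 20 women, so this can only be supportive.

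**Reporting.** Unless enough women have a pre-dose score, word conclusions as symptoms during tamoxifen, not tamoxifen-induced.

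**Cost.** An ethics amendment, and some women missed because they cannot be approached at the prescribing visit. No assay is added; an existing questionnaire moves earlier. Recruitment began in November 2016, and at the expected 100 to 150 women a year, 200 would take 16 to 24 months. Few recruits may therefore remain, and the timing, covariate and wording changes may be all that is still possible.
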